## Abstract

**Background:**

The HOME^ONE^ study is part of the larger *HOME* project, which aims to provide evidence of diagnostic and therapeutic yield (“change of management”) of a patient-controlled portable EEG device with dry electrodes for the purposes of EEG home-monitoring neurological outpatients.

**Methods:**

The HOME^ONE^ study is the first step in the process of investigating whether outpatient EEG home-monitoring changes the diagnosis and treatment of patients in comparison to conventional EEG (“change of management”). Both EEG devices (conventional and portable) will be systematically compared via a two-phase intra-individual assessment.

In the first phase (pilot study phase), both EEG devices will be used within neurologist practices (all other things being equal). This pilot study (involving 130 patients) will evaluate the technical usability and efficacy of the new portable dry electrode EEG recorder in comparison to conventional EEG devices. Judgements will be based on technical assessments and EEG record examinations of private practitioners and two experienced neurologists (percent of concordant readings and kappa values).

The second phase (feasibility study phase) aims to assess patients’ acceptability and feasibility of the EEG home-monitoring and will provide insights into the extent diagnostic and therapeutic yields can be expected.

For this purpose, a conventional EEG will be recorded in neurologist practices. Thereafter, the practice staff will instruct the patients on how the portable EEG device functions. The patients will subsequently use the devices in their home environment.

The evaluation will compare the before and after documented diagnostic findings and the therapeutic consequences of the private practitioners with those of two experienced neurologists.

**Discussion:**

To the best of our knowledge, this will be the first study of its kind to examine new approaches to diagnosing unclear consciousness disorders or other disorders of the CNS or the cardiovascular system through the use of a patient-controlled portable EEG device with dry electrodes for the purpose of home-monitoring neurological outpatients. If the two phases of the HOME^ONE^ study provide sufficient evidence of diagnostic and therapeutic yields, this would justify (indication-specific) full-scale randomized controlled trials or observational studies.

**Trial registration:**

DRKS DRKS00012685. Registered 9 August 2017, retrospectively registered.

## Background

At present, EEGs can only be recorded with considerable effort over a prolonged period of time under the everyday conditions of the patient. Patients are also unable to place an EEG cap on their own. To address these issues, a portable dry electrode EEG recorder (Fourier One) was developed. This new EEG device, which is integrated into a patient-friendly cap, records brain waves continuously or patient-controlled over a longer period of time. The patient can place the portable EEG device independently without the help of medical staff. With the development of this new EEG device, it is also possible to record brain waves outside medical facilities over a period of time ranging from several hours through to days under everyday conditions in the patient’s home. This results in new possibilities for the differential diagnosis of suspected cases of epilepsy, unclear consciousness disturbances, sleep disturbances, ADHD, or other disorders of the CNS, in contrast to other causes. The use of the new EEG device might also result in changes in the therapeutic management (e.g., changes in medication). These possible changes are summarized under the term “change-of-management” and reflect the therapeutic yield of a patient-controlled EEG home-monitoring. In this regard, the new portable dry electrode EEG recorder is intended to be used for both diagnostic performance and part of the therapeutic management.

Traditional EEG devices are not intended to be used in the home environment of patients, especially due to their immobility. To meet medical and technical requirements and the needs and expectations of patients and professionals, Pinho et al. [1] summarize that EEG systems for outpatient care shall have the following features: “wireless connectivity, dry electrodes, signal resolution, sampling frequency, comfort, portability, signal artefact attenuation, event detection and event prediction” (p. 565). For the purposes of realizing the *HOME* project, we expand the list of necessary features by adding two additional needs: (1) an integrated and structured reporting system and (2) the full coverage of the 10–20 system for electrode placement. There are several EEG devices on the market that meet (at least some of) these demands (e.g., [2–5]); other devices are in the developing process (e.g., [1, 6, 7]). The “Fourier One”^1^ was developed to fulfill all demands and is, to the best of our knowledge, the first that meets all legal requirements (particularly with regard to CE certification) for the use in routine medical care and for home-monitoring.

The Fourier One cap (F1) is a CE-approved^2^ medical device of class IIa. With electrodes located at the EEG typical positions (10–20 system), it has the same technical monitoring and evaluation possibilities as a conventional practice EEG device. Since brain waves can also be recorded under everyday conditions, the cap has a wider range of applications than a conventional practice EEG. The signals are digitized by miniaturized electronics and stored on a chip that is integrated into the cap. The chip is read in the supervising neurological practice. The technical signal quality facilitates the diagnostic assessment of brain waves, which corresponds to the conventional EEGs. A telemedical transmission of the brain waves is generally possible but has yet to be realized.

### Objectives of the *HOME* project and specific objectives of the HOME^ONE^ study

The goal of the *HOME* project is to implement an EEG home-monitoring system with a patient-controlled portable dry electrode EEG recorder for use within the routine care of outpatients (for diagnostic purposes as well as for therapeutic management). The HOME^ONE^ study will be a two-phase (pilot study phase and feasibility study phase) intra-individual comparison that is driven by the following aims:To evaluate the technical usability and efficacy of the new portable dry electrode EEG recorder in comparison to the conventional EEG devices (pilot study phase);

To determine whether the pilot study objectives are met, we will analyze the technical assessments and EEG record examinations of the private practitioners and two experienced neurologists (percent of concordant readings and kappa values). After the technical usability and efficacy are shown, the second HOME^ONE^ study phase will be conducted. This feasibility study will aim to:(2)Assess patients’ acceptability and the feasibility of the EEG home-monitoring (feasibility study phase);(3)Provide insights into the extent of expectable diagnostic and therapeutic yields (feasibility study phase).

To evaluate whether this feasibility study was successful, we will analyze the before and after documented diagnostic findings and the therapeutic consequences of the private practitioners and compare them with those of two experienced neurologists. As is the case in the pilot study phase, a technical assessment is also part of the analyses.

If the two phases of the HOME^ONE^ study provide sufficient justification for technical usability, practical feasibility, and diagnostic and therapeutic yields, this will justify (indication-specific) full-scale randomized controlled trials or observational studies.

To realize the goals of the *HOME* project (and the HOME^ONE^ study), which is being performed by the University Department of Neurology Magdeburg, we established a network of practices of neurologists in Saxony-Anhalt, a federal state of Germany.

## Methods/design

### Study phases and settings

The portable EEG monitoring will be performed with patients of neurologist practices. A total of 18 participating specialists from the Saxony-Anhalt region have agreed to the study concept, including an advisory second opinion by the University Department of Neurology Magdeburg (KNEU). The practicing neurologists remain responsible for the medical care of their patients.

The HOME^ONE^ study consists of two phases:

During the *pilot study phase* (first phase), an EEG examination with the portable EEG system (F1) will be carried out with a population of approximately 130 study patients in addition to the conventional EEG approach *in the practices of* private practitioner*s*. As such, two EEG recordings will be performed during one consultation (but in sequence) with all other things being equal. This phase will examine the technical usability and efficacy of the new portable dry electrode EEG recorder and compare it with the different conventional practice EEG devices. It will also draw conclusions about the conformity of the reporting physicians. It is, hence, useful to “calibrate” the physicians, especially those from the KNEU who are responsible for performing the second assessment, before the beginning of the second phase. The inter-rater reliability of EEG evaluations shows kappa values of 0.5 to 0.9 [8–11], depending on the question. As an example, experienced epileptologists feel safe in their findings but have only low inter-rater matches [12]. It cannot be excluded that the additional use of the portable EEG device in neurological practice can already provide a diagnostic, therapeutically useful gain in knowledge.

During the *feasibility study phase* (second phase), the EEG examination will be carried out with approximately 500 study patients. This will commence with a conventional EEG in the doctor’s practice. Subsequently, the neurological practice will introduce the patient to the functioning and handling of the portable EEG device and the necessary accessories. Afterwards, the patient will be able to independently place and remove the portable EEG device and to use it in his or her home environment according to the dispositions of the neurologist.

The doctor in charge will determine the recording time with the cap according to medical criteria. The effective recording time will be included in the empirical evaluation.

The feasibility phase will serve to evaluate patients’ acceptability and feasibility of the EEG home-monitoring process. In addition, this study will aim to generate initial insights into the extent to which EEG home-monitoring achieves the expected diagnostic and therapeutic yield with regard to the use of a patient-controlled, portable EEG device with dry electrodes for home-monitoring of neurological patients.

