### Target group, inclusion and exclusion criteria

The study will include patients (male and female of the age of 18 or older) who, according to the judgment of the practicing neurologist, have a suspected or manifest disease giving rise to the medical indication to record an EEG (first or repeated) within the framework of usual statutory care (i.e., billing numbers EBM 16310 or 16311). The private practitioner will be responsible for the selection and the information of the patients.

In both study phases, patients who have to be treated after the first EEG due to hazard prevention will not be included in the study. In addition, patients under the age of 18 will be excluded.

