### Indication, implementation, and evaluation of EEGs

Before using the conventional EEG, the private practitioner will document the diagnostic question and the therapeutic options. This will serve as the proof for the indication of the conventional EEG. The private practitioner will also document the patient’s medical history.

Both the conventional practice EEG and the portable EEG will be derived in the pilot study phase (first phase) according to uniform standards over 20 min as per the German Society of Clinical Neurophysiology (DGKN) guidelines [13].

In the feasibility study phase (second phase), the EEGs will be derived according to the guidelines of the German Society of Clinical Neurophysiology (DGKN) [13, 14] per the neurologist (possibly also as long-term EEG). The portable EEG will be stored on a memory card that is integrated into the headset. The patients will return with the headset and activity and evaluation sheet, which they will be required to complete.

Subsequently, in both phases of the HOME^ONE^ study, the private practitioner will examine both EEGs using the same standardized assessment sheet.

Both results will be collected by a staff member of KNEU. In the run-up to the second assessment of both EEGs, the Data Trustee will transfer the data from the conventional EEG devices into the standardized format of the portable EEG device and will blind all EEGs. The blinded EEGs will then be examined by two experienced neurologists from KNEU.

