### Data analysis and measures

Comparing the two EEG recording methods, the conventional practice EEG cannot be the gold standard to determine the sensitivity, specificity, and predictive values of the portable EEG. The goal that underpins the use of the portable EEG is to gain additional diagnostic insights through extended use. However, in the present state of the method, the portable EEG can remain behind the conventional practice EEG in its diagnostic yield, for example, due to increased artifacts or errors in handling by the patient. As such, it will be necessary to document the technical assessment and the extent to which there is concordance between the two EEGs.

In the pilot study phase, all three assessors will evaluate the technical quality of the EEG records according to the following ratings:The EEG record is unrestrictedly for medical reporting,The use of the EEG record for medical reporting is limited, andThe EEG record is not usable for medical reporting.

The evaluation of the technical quality is based on different criteria:The assessor’s overall impression on the EEG record,The frequency of artifacts,Strength of 50 Hz line noise, andRecovery of EEG traces after strong artifacts.

These criteria meet the standards of the International Federation of Clinical Neurophysiology (IFCN) for digital recording of clinical EEG [15].

In addition, all three assessors will document their medical reports for each blinded EEG record. After re-identification of the EEGs and the associated medical reports by the Data Trustee, the concordance (or discordance) will be evaluated. As measurements, we will use concordance rates and kappa values.

In the feasibility study phase, we will use the same approach. However, we will extend it as follows: To share information regarding a possible change of management, the private practitioner will classify the results of the conventional practice EEG according to the possibilities presented in Table 1.

**Table 1 Tab1:** Action-oriented classification of the findings of the conventional practice EEGs

1A	No action or follow-up appointment only
1B	Targeted referral for further clarification or co-treatment or further treatment
1C	Initiate or change therapy (adjust, switch, settle)

In the same way, they will also classify the results of the portable EEG (see Table 2).

**Table 2 Tab2:** Action-oriented classification of the results of the portable EEG

2A	No action or follow-up appointment only

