### Sample size calculation

#### Pilot study phase

Because the judgements in this study phase will be mainly based on inter-rater reliability, we will calculate the sample size regarding this issue. According to [16], we will assume a difference between the overall agreement probability and the chance agreement probability of 0.3 and a relative error of 0.3. This will lead to a sample size of 123 subjects. For the pilot study phase, therefore, we expect there to be a duplicate diagnosis for 130 patients.

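### The pilot asserts equal conditions for two sequential recordings without stating a balanced order, and its named measures (concordance, kappa) show neither the level of usability nor which device is worse

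*Protocol article*

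**What the plan says.** **Recording layout.** Under Study phases and settings, the pilot uses the portable cap "in addition to the conventional EEG approach", and "two EEG recordings will be performed during one consultation (but in sequence) with all other things being equal". Under Indication, implementation, and evaluation of EEGs, both pilot recordings are made "according to uniform standards over 20 min".

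**Order.** No section states a randomised or counterbalanced recording order. Three places lean towards conventional first: the wording just quoted on adding the cap; the documentation step, "Before using the conventional EEG, the private practitioner will document the diagnostic question and the therapeutic options"; and an exclusion for both phases, under which "patients who have to be treated after the first EEG due to hazard prevention will not be included in the study". The only randomisation described (Randomized second assessment by KNEU) concerns how pseudonymised records are handed to the two university readers.

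**Measures.** Under Data analysis and measures, "In the pilot study phase, all three assessors will evaluate the technical quality of the EEG records according to the following ratings"; the scale has three levels, from fully usable to not usable. The summary measures named there and in the Objectives section are concordance rates and kappa values. The pilot sample size section adds: "Because the judgements in this study phase will be mainly based on inter-rater reliability, we will calculate the sample size regarding this issue".

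**Role of the pilot.** The Objectives section sets the aim as usability and efficacy relative to conventional devices, and starts the second phase "After the technical usability and efficacy are shown".

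**The concern.** There are two linked problems.

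First, if recordings follow one another, position in the visit is itself a difference between devices unless order is balanced. The patient may be drowsier or more used to the procedure by the second recording, and the scalp may have been prepared or disturbed by the first. The equality claim assumes this away.

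Second, the pilot's question is directional: is the cap's record as usable as the conventional one? Agreement between readers, and undirected concordance between devices, do not answer it. In addition, the section on the second assessment removes from the further method comparison any patient with at least one technically unassessable EEG, and does not limit that rule to one phase. Cap failures would therefore leave the concordance analysis, and would be visible only in the technical ratings, for which no device contrast is named.

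At stake is the decision to proceed to a phase of about 500 patients.

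**Working it through.** **1. The plan's own figure.** Inputs from the pilot sample size section: a difference between overall and chance agreement of 0.3, and a relative error of 0.3.

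n = 1/(0.3² × 0.3²) = 1/0.0081 = 123.46

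The stated 123 reproduces, and 130 are planned. It is a precision target for reader agreement, not for a difference between devices.

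**2. Kappa does not fix the level of usability.** Take two readers who each call a share p of records unusable, with raw agreement po. Chance agreement is pe = p² + (1−p)², and kappa = (po − pe)/(1 − pe). The values of p and po are assumed.

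- p = 0.50, po = 0.90: pe = 0.50, kappa = 0.40/0.50 = 0.80
- p = 0.10, po = 0.964: pe = 0.82, kappa = 0.144/0.18 = 0.80

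The same kappa goes with 50% and with 10% unusable records.

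**3. Kappa and concordance between devices have no direction.** In a fourfold table of proportions with discordant cells b and c, raw concordance is a + d and chance agreement is (a+b)(a+c) + (c+d)(b+d). Exchanging b and c changes neither, so a worse cap and a better cap can give the same values. A directional paired test (McNemar) is named only for the feasibility phase.

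**4. Order.** Let D be the device difference, P an additive second-position effect, and s the share of patients with the cap second. The expected observed difference is D + P(2s − 1). The documents give no P. For an assumed P of 10 points:

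| s | bias (points) |
|---|---|
| 1.00 | 10 |
| 0.90 | 8 |
| 0.75 | 5 |
| 0.50 | 0 |

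With s = 1, a true difference of +10 and a position effect of −10 would show as 0. With D = 0, s = 1, 130 pairs and assumed discordance of 20%, a two-sided 5% paired test would show a device difference in about 25% of pilots for P = 5 points, and about 73% for P = 10 points. These are illustrations, not estimates.

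**5. What 130 pairs can deliver on the paired difference.** The 95% half-width around zero difference is 1.96 × √(q/130), with assumed discordance q:

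- q = 0.10: 1.96 × 0.0277 = 5.4 points
- q = 0.20: 1.96 × 0.0392 = 7.7 points
- q = 0.30: 1.96 × 0.0480 = 9.4 points

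**The case against.** The strongest reply is that usability is rated directly: three assessors grade every record on artifacts, line noise, trace recovery and overall impression, and the Objectives section lists technical assessments among the evidence. This stands. A reader might infer that a cap which everyone agrees is unusable would pass unnoticed. The documents do not support that, because such a result would appear in the ratings. What remains is that the ratings have no named device contrast, while the article itself names other measures and says which one mainly carries the judgement.

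A reader might also infer that the order is fixed, or that the pilot cannot isolate the device effect at all. Neither is supported. A fixed order is suggested but never stated, and the full protocol may set the order. Patient, visit, duration and recording standards are shared, and some criteria, such as 50 Hz noise, are not obviously driven by position. Even so, the equality claim is a positive statement in the article, and the layout described does not secure it.

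Sizing on reader agreement also serves a stated purpose, since the pilot is meant to assess and calibrate the readers. That is a reason to keep kappa, but not to let it stand for usability. Finally, no numerical threshold for proceeding is given, so the direction in which an order effect would move the decision is unknown.

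**Conclusion.** The point holds in a limited form and should be corrected; no stated number is wrong. As described, device and position are not separated, and blinded, randomised reading cannot remove an effect already in the trace. The named pilot measures do not match a comparative usability aim, although the data that would match it are already to be collected.

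The size of any order effect is unknown, and the half-widths of 5.4 to 9.4 points must not be read as one. They describe only sampling precision under assumed discordance of 10 to 30% and a difference near zero. The order calculation assumes an additive position effect that is the same for both devices.

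**What to change.** 1. Make the pilot's usability measure the within-reader paired difference, cap minus conventional, in the proportion of records rated fully usable and in the proportion rated not usable, each with a 95% CI. Include all recorded patients, also those with an unassessable record. Keep inter-rater kappa for reader calibration.
2. Randomise recording order 1:1 (about 65/65), or at least note the order for each patient and report the comparison by order. If neither is done, drop the equality claim. Balance removes an additive position effect on average; it does not remove carry-over that differs by which device came first.
3. Reconcile the exclusion that refers to the first EEG with the recording order chosen. Under random order the first recording would be the cap for about half the patients, so the sponsor must say which recording the wording means.

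The cost is an order list, a small scheduling burden in the practices, one clarified sentence and one extra table from ratings already planned. The sample size stays at 130.
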